### Primary objectives

To estimate the difference in wellbeing scores at baseline versus the endline among caregivers in the intervention versus control armTo ascertain the percentage of potential participants that both meet the eligibility criteria and enrol in the studyTo determine the participant recruitment and retention rateTo establish compliance with the intervention processPiloting the methodological procedures, including randomisation, telephonic interviews, electronic data collection and electronic intervention deliveryTo reflect on the intervention protocol and amend as neededTo describe participants’ views on acceptability by exploring their experiences of participating in the trial, assessing trial processes (content, delivery, utilisation, safety), and outcome measures

### Secondary objectives

To examine the relationship between stigma, food insecurity and wellbeingTo understand experiences of caregiver wellbeing and whether or not economic incentives shaped these experiencesTo estimate the total cost of delivery of the economic incentive and the average cost per person with an increase in caregiver wellbeing score in the intervention versus control armConduct a power calculation to determine the numbers needed for a large-scale RCT

## Methods

Reporting and methodology for the proposed study follow the Standard Protocol Items Recommendations for Interventional Trials (SPIRIT) [54] (see Fig. 1), as well as Consolidated Standards of Reporting Trials (CONSORT)—extension to randomised pilot and feasibility trials [55] (Additional file 4: Appendix 4). The intervention has been reported using the Template for Intervention Description and Replication (TIDieR) [56].

**Fig. 1 Fig1:**
[figure not shown]
Standard protocol items: recommendation for intervention trials (SPIRIT) flow diagram

### Design

This will be a two-group parallel, open label pilot RCT. The study will have two arms, an intervention group (*n* = 50) and a control group (*n* = 50).

### Setting

This study will be conducted in a peri-urban community within the south of the eThekwini municipality, KwaZulu-Natal, South Africa. Recruitment, baseline quantitative assessments, and qualitative interviews will be conducted face-to-face. Whereas intervention delivery and end of trial assessments will be conducted telephonically.

### Participant recruitment

Participants will be recruited via:An existing study database of caregivers of ALHIV who were enrolled in an adolescent studyInformation sessions within local HIV clinics

### Participant eligibility criteria

Participants will be eligible to participate in the trial if they meet the following criteria:Caregivers (≥ 18 years of age) of ALHIV aged 10–19 yearsCaregivers who have their own personal mobile phone to ensure that there are no unauthorised cash withdrawals as the pin for retrieving the cash will be delivered to their mobile phone.

Participants will be excluded from the study should they have any of the following:Caregiver who is unable to comprehend the nature of the study during the information session in either English or isiZuluA caregiver who is experiencing distress, suicidal ideation, or requires urgent medical attentionA caregiver who *does not* have their own personal mobile phone

### Screening

Initial contact will be face-to-face at the study clinic. Participant eligibility will be assessed, followed by explanation of the study, assessment of study understanding, and completion of consent procedures (Additional file 1: Appendix 1).

### Baseline and endline assessment

Post-screening, a baseline assessment will be conducted (Additional file 2: Appendix 2). After the intervention period, the endline assessment will be conducted. For the assessments, the following data will be collected on an electronic interviewer-administered REDCAP questionnaire:*Socio-economic status* (e.g. demographics, dwelling type, household occupants, household dwellers’ ages), labour and income (e.g. employment status, income range), and household and social outcomes (e.g. number of children on support grants, source(s) of income).*Food security* will be assessed using the Food Insecurity Experience Scale (FIES). The FIES has demonstrated good internal reliability in this setting (Rasch reliability infit statistic > 0.7) [57].*Depressive symptoms* will be measured using the 10-item Centre for Epidemiological Studies Depression Scale (CES-D-10). The CES-D-10 has been psychometrically evaluated in a South African sample and showed acceptable internal consistency across different language groups (Cronbach’s α = 0.69–0.89), and concurrent validity when compared to other depressive symptom measures commonly used (e.g. Patient Health Questionnaire, WHO Disability Assessment Schedule) [58]. The scale has also shown good convergent validity (regression co-efficients between known psychosocial measures and EDS ranged from 0.17 to 0.19, *p* < 0.001) [59] and internal reliability (Cronbach’s α = 0.86) [60]. A cut-off point of 12 is deemed optimal to correctly classify individuals with a diagnosis of depression for a South African sample [61].*Stigma:* the Everyday Discrimination Scale is a recommended scale for measuring intersectional stigma, particularly among people living with HIV [62], and has demonstrated good psychometric properties in samples from the United States of America [63].

#### Primary clinical outcome measures informing our sample size

Percentage change in wellbeing scores pre-vs. post-intervention:*Wellbeing* will be measured using the Care-related Quality of Life (CarerQol) instrument. The CarerQol instrument is a preference-based measure that was developed for use in economic evaluations [64], and has exhibited moderate construct validity (correlation co-efficient with CarerQol and self-rated burden dimensions ranging from 0.2 to 0.4) among older carers in the Netherlands [65]. Clinical and convergent validity have also been supported [66].Successful consent rate: a minimum of ≥ 80% of eligible participants enrolled in the studySuccessful retention rate: a retention rate of ≥ 80% of recruited participants

### Randomisation and allocation concealment

A statistician on the research team who is not involved in the intervention or outcome measure assessments will randomly allocate participants to the intervention or control group. The randomisation list will be generated in STATA (Stata Corp, College Station, TX, V17) using block randomisation techniques. This method is used to ensure a sample size balance across groups over time. Blocks will be small and balanced with predetermined group assignments, which keeps the numbers of subjects in each group similar. A seed will be used for the reproducibility of the same randomisation output obtained. Block randomisation with randomly selected block sizes of 2, 4, 8, and 12 will be generated. Four blocks of equal size (*n* = 25) will be generated in STATA, with two blocks assigned to each study arm (i.e. intervention: n=2 × 25 = 50; control: *n* = 25 × 2 = 50) and the list exported to Excel. This list will be emailed to a second researcher who will assign the intervention or control programme to each participant.

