### Blinding

This is an open label trial as field staff will be involved in the intervention delivery and study assessments. The statistician involved in the randomisation will be blinded to study arm. Participants will be encouraged not to disclose details regarding their wellbeing programme to other participants during the trial. We will at multiple points (consent, baseline interview, cash send, follow-up) encourage participants not to share their study details, including randomisation, to anyone else.

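### The researcher who assigns participants is emailed the full allocation list, with no stated separation from enrolment and no release rule, so the described procedure does not secure concealment

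*Protocol article*

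**What the plan says.** All references are to the protocol article.

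- **Randomisation and allocation concealment**, on who makes the list: "A statistician on the research team who is not involved in the intervention or outcome measure assessments will randomly allocate participants". The list is made in Stata.
- **Same section**, on its structure: "Block randomisation with randomly selected block sizes of 2, 4, 8, and 12 will be generated". The next sentence describes four blocks of 25, which "will be generated in STATA, with two blocks assigned to each study arm".
- **Same section**, on the handover: the totals are 50 per arm, the list goes to Excel, and then "This list will be emailed to a second researcher who will assign the intervention or control programme to each participant". No other step lies between the list and the participant.
- **Blinding**: "This is an open label trial as field staff will be involved in the intervention delivery and study assessments". The statistician is said to be blinded to study arm. Participants are asked at several contacts, including consent and the baseline interview, to keep their study details and randomisation to themselves.
- **Screening**: "Initial contact will be face-to-face at the study clinic". Eligibility, explanation, a check of understanding and consent follow. The staff role is not named.
- **Participant eligibility criteria**: the exclusions include inability to comprehend the study and being in distress, both of which need a judgement by the person screening.

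**The concern.** Allocation concealment means that whoever decides on a person's entry cannot foresee that person's arm. It does not require blinding, so an open-label trial comparing cash with no cash can still achieve it. Here the section that carries the term in its heading gives the complete sequence to the person who makes each assignment, and states nothing that keeps knowledge of the next assignment away from the decision to enrol.

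If the list holder screens, or passes the next assignment to those who do, a caregiver seen as needier could be enrolled, deferred or judged ineligible according to the arm that comes next. Randomly varied block sizes give no protection against someone who has the list.

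The stakes go beyond this sample. Piloting the methodological procedures, randomisation among them, is a primary objective, and the pilot is meant to shape a larger trial that would inherit the same handover. The wellbeing comparison between arms is also listed as a primary objective.

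**Working it through.** The point is mainly procedural, so the first step sets the statements side by side. The counts that follow show only how predictable assignments are.

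**1. Which safeguards are stated, and for whom**

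| Safeguard | Statistician | Second researcher (assigns) |
|---|---|---|
| Not involved in intervention or outcome assessment | Stated | Not stated |
| Not involved in screening or enrolment | Not stated | Not stated |
| Sees only one assignment at a time | Does not apply (makes the list) | No; receives the list |
| Assignment only after consent and baseline are recorded | Does not apply | Not stated |

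The handover is positively described, and no stated safeguard applies to the person who receives the list.

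**2. The plan's own totals.** Four blocks of 25 give 4 × 25 = 100, and two per arm give 2 × 25 = 50. This reproduces the 50 per arm in the Design section.

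**3. Predictability with the list.** If the arms are labelled, the holder knows 100 of 100 assignments.

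**4. Predictability without the list, random blocks of 2, 4, 8 and 12.** The guesser sees past assignments and names the arm with fewer participants so far, tossing a coin when the arms are equal. Over 10,000 simulated lists of 100, the mean was 66.6 correct, or about 67 of 100. This is a benchmark for ordinary guessing in an open-label trial; it does not measure the harm of the emailed list.

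**5. Predictability without the list, four blocks of 25 read literally.** Suppose each block is wholly one arm and the guess is always the same arm as the last participant.
- The six possible orders of two intervention and two control blocks have 1, 1, 2, 2, 3 and 3 changes of arm. The mean is 12/6 = 2.
- The first guess is wrong half the time.
- Expected correct guesses: 100 − 2 − 0.5 = 97.5. The simulation gave 97.5.

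**6. Consistency of the two block descriptions.** Sums of 2, 4, 8 and 12 are always even, so such blocks cannot fill a block of 25. The two descriptions conflict, and the block scheme cannot be relied on as a second line of protection until they are reconciled.

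**The case against.** **Holding the list is not the same as breaking concealment.** An office-based researcher who assigns only after enrolment, and has no contact with screening, can keep allocation fully concealed from recruiters. The article describes screening separately and gives delivery and assessment to field staff. This stands. A reader might infer that allocation was in fact unconcealed, but the article does not say that the second researcher screened or enrolled anyone.

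**Timing and format are inferred.** That the list was sent before enrolment began is a fair reading of a list sent to someone who will assign, but it is not stated. Nor is it stated that the arms were labelled; the remark that the statistician is blinded to study arm could fit a coded list. This also stands, and the count of 100 of 100 depends on it. However, the person who assigns must at some point be able to decode the list.

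**A journal article condenses.** The second researcher's duties may be set out in the full protocol, and silence alone would be no finding. This stands only in part. The article gives concealment its own section, and the mechanism written there is the emailed list. The criticism is of that stated mechanism.

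**Baseline scores would expose or remove the bias.** A reader might infer that selection could not be told apart from an intervention effect. That goes too far. Wellbeing is measured at baseline, the Statistical analysis section compares change from M1 to M5, and baseline variables that differ between arms become covariates. Steering by wellbeing would tend to appear as baseline imbalance and be partly removed. Regression to the mean and unmeasured differences would remain, so the protection is partial.

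**Limited consequence.** Enrolment and follow-up are complete, the progression criteria rest on overall enrolment and retention, and the Limitations section says caregivers were drawn consecutively, which leaves less room for steering. All of this lowers the weight of the point for the pilot. It does not affect the objective of testing randomisation for a larger trial.

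**Conclusion.** The point holds in this form: the procedure written under allocation concealment does not secure concealment. The person who assigns has the whole list, no text separates that role from screening and enrolment, and no text makes assignment follow recorded consent and baseline. Open-label delivery and judgement-based exclusions make this matter.

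In terms of predictability, the list holder knows 100 of 100 assignments, against about 67 for a guesser under the random block sizes. The first figure assumes that the arms are labelled and the list is sent before enrolment ends; the second assumes that the guesser sees all past assignments. Under the literal blocks of 25, even a guesser without the list would be right about 97 times in 100.

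The size of any bias in the wellbeing comparison cannot be derived. It would need assumptions about how many caregivers were steered and how different they were. An imbalance in score level also cannot be set against the 2.0-point gain in the Sample size section (6.5 to 8.5), which is a within-arm change over time. This is a worthwhile, inexpensive improvement, and no evidence that the pilot's results are biased.

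**What to change.** **Main trial.** Replace the emailed list with release of one assignment at a time, only after eligibility, consent and baseline are recorded. Either of two routes will do: the randomisation module of REDCap, the system already used for the questionnaires, or the statistician keeping the list and sending each assignment on request. State that whoever holds the sequence has no part in screening, consent, baseline or outcome assessment. Reconcile the two block descriptions at the same time.

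**Completed pilot.**
1. Report who held the list, when it was sent, whether the arms were coded, and whether that person had any part in screening or enrolment.
2. Compare REDCap consent and baseline timestamps with list order (using the consent record itself if consent was not captured there), and report every out-of-sequence assignment. This check can show reordering. It cannot show a caregiver turned away because of the next assignment, so the answer to step 1 is still needed.
3. Do not describe allocation as concealed unless the list holder had no part in screening or enrolment. Otherwise, add weak concealment to the limitations, which at present mention only the lack of blinding.

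**Cost.** A REDCap set-up or one short message per participant, a short wait for each assignment, a brief timestamp audit, and one or two sentences in the report.

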### Blinding

This is an open label trial as field staff will be involved in the intervention delivery and study assessments. The statistician involved in the randomisation will be blinded to study arm. Participants will be encouraged not to disclose details regarding their wellbeing programme to other participants during the trial. We will at multiple points (consent, baseline interview, cash send, follow-up) encourage participants not to share their study details, including randomisation, to anyone else.

### Intervention

Participants in the intervention group will receive an economic incentive package comprising a monthly motivational SMS and cash to the value of ZAR 350 (23 USD) for three months. The SMS will promote key behavioural economic principles (aspiration framing, loss aversion, altruism), aligned to social wellbeing dimensions that matter to people in this context (Table 1) [67]. The R350 incentive amount was chosen because it is within the margin of the COVID-19 Social Relief of Distress (SRD) grants in South Africa [68]. Participants will have 30 days to claim the receipt of their cash. It will be delivered via electronic local banking services. In line with the human centred design (HCD) approach, themed nudge messages will be co-developed with a caregiver advisory board (CAB), revised and used by the research team to design SMS messages to be sent to participant’s mobile phone via SMS by designated research team members using a standardised message template. The CAB will comprise 16 caregivers of ALHIV, who will not be part of the trial but from study community. The role of the CAB will include to inform study design, advising on intervention implementation, participant retention strategies, reviewing key findings, assisting with interpretation and dissemination of findings.

**Table 1 Tab1:** Intervention messages and underpinning behavioural economic principle

Message	Behavioural economic principle	Message content
1	Aspiration framing	“Taking care of your own needs is important so you can be there to watch your child grow”
2	Loss aversion	“If you need to speak to someone you can call the South African Depression and Anxiety Group at no cost to you (Number:)”
3	Altruism	“Taking care of your child and family’s needs are important”

### Control

The control group will receive a once-off SMS encouraging access to public health clinic services as per the standard message sent by the Department Health in South Africa to patients accessing clinic services. Participants in this group will not receive cash or a motivational SMS.

### Qualitative study

A subset of participants in the intervention (*n* = 8) and control (*n* = 8) arm will be invited to participate in in-depth interviews after their baseline and endline quantitative assessments. They will be purposively sampled to ensure the sample is reflective of age, socio-economic status and HIV status. The aim of these IDIs is to provide an authentic account of wellbeing experiences among caregivers in this setting [69], to understand how experiences differ by arm and what could explain these differences. Topic guides (Additional file 3: Appendix 3) will be mapped on dimensions from our wellbeing scales (e.g. financial problems, relational problems, household and caregiving chores, mental and physical health, belonging) and preliminary findings from the trial. For those in the intervention arm, specific elements regarding the intervention will be probed as part of endline in-depth interview (i.e. timing, cash incentive amount, delivery method, safety concerns, SMS content, utilisation of the cash incentive, access of mental health support, recommendations to improve the intervention).

### Sample size

Our primary outcome is pre-post between difference in caregiver wellbeing scores. Assuming a mean caregiver wellbeing VAS score of 6.5 in M1 versus 8.5 in M5 (SD1.9) in the intervention arm, we would need a minimum sample size of *n* = 15 per arm to have 80% power to detect a treatment effect of between δ = 0.6–0.5 [66, 70]. Thus a sample size of *N* = 100 will satisfy this primary outcome and give us enough sample to look at feasibility measures (consent and retention rate ≥ 80%), assuming *n* = 20 refuse to participate or are lost to follow-up.

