### Limitations

The trial will be subject to the following limitations: (1) the sample will comprise a select group of caregivers consecutively drawn from an existing study database and approached during clinic appointments, limiting the generalisability of our findings; (2) whilst the wellbeing and other key measures have exhibited good psychometric properties, the isiZulu versions of these scales are yet to be robustly evaluated for this setting; (3) it is highly probable that the cash incentive value may be insufficient to impact wellbeing. However, the value of the cash incentive is higher than that used in previous studies which have shown promising effects on HIV care outcomes; (4) the duration of the intervention may be too short for individuals to change behaviours and make major shifts in their wellbeing; (5) a two-armed trial (cash + SMS versus control), does not allow us to specifically examine the effects of individual intervention components on wellbeing. However, the qualitative study will probe specific elements of the intervention, and this will provide some idea on how each component facilitated wellbeing; (6) participants will not be blinded to trial arm. However, participants will be encouraged not to disclose their programme randomisation status to other participants at each stage of contact (i.e. consent, baseline interview, cash send delivery, follow-up interview); (7) although study sample size was sufficient to generate 80% power to detect treatment effects, this sample size might not be sufficient to extrapolate statistical analysis results that are generalisable over the entire ALHIV caregiver population; and (8) the lack of blinding could add bias to findings. It is, therefore, recommended that future full-scale trials use a cluster RCT approach to minimise bias.

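### The claim that 15 per arm gives 80% power for δ = 0.5–0.6 does not match its own inputs, which imply 1.05 SD; as a standardised difference, 0.5–0.6 needs 64 to 45 per arm

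*Protocol article*

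**What the plan says.** All planning figures are in the Sample size section of the protocol article.

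- The outcome: "Our primary outcome is pre-post between difference in caregiver wellbeing scores".
- The planning values: "Assuming a mean caregiver wellbeing VAS score of 6.5 in M1 versus 8.5 in M5 (SD1.9) in the intervention arm".
- The claim: a minimum of "15 per arm to have 80% power to detect a treatment effect of between" δ = 0.6–0.5.
- The total of 100 is then said to satisfy this outcome and to leave enough for the feasibility measures, on the assumption that 20 people "refuse to participate or are lost to follow-up".

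The section does not define δ, alpha, sidedness, the change expected in controls or a baseline–endline correlation. It does not say whether 1.9 is the SD of the score or of the change. The Statistical analysis section compares the change in score between arms by linear regression. Limitation 7 repeats the conclusion without naming an effect: "although study sample size was sufficient to generate 80% power to detect treatment effects".

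**The concern.** One sentence carries two effect sizes that differ by a factor of about two: 2.0/1.9 = 1.05 SD in its inputs, and 0.5–0.6 in its claim. Sample size goes with the inverse square of the effect, so the number needed differs about fourfold. A reader cannot tell whether the pilot was sized for roughly half an SD or for a full SD.

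Two further features weaken the calculation whatever δ means. The 2.0 points is a change over time within one arm, but the outcome is a comparison between arms. And the 20 combines people who decline with people who drop out, although only the second group can reduce the 50 + 50 randomised.

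What is at stake is how the wellbeing result is read. It is the first primary objective, and the Discussion allows for a finding of no effect. With an unqualified 80% power statement, such a finding could be taken as an adequately powered null for effects that 15 per arm could not reliably detect.

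**Working it through.** **Inputs from the Sample size section:** means 6.5 and 8.5 (difference 2.0 VAS points), SD 1.9, 80% power, 15 per arm, δ = 0.5–0.6, 20 of 100 not available. **From the Design section:** 50 per arm. **Assumed, because not stated:** two-sided 5%, independent groups, no gain from baseline data.

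**1. Reproduce the stated 15.** By the normal approximation, n per arm = 2(z₀.₉₇₅ + z₀.₈₀)²·SD²/Δ².

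2 × (1.96 + 0.8416)² × 1.9²/2.0² = 14.17, rounded up to 15 (16 by the t-test).

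The stated 15 therefore follows from 2.0/1.9 = 1.05 SD. Power at 15 per arm for that effect is 82% by the normal approximation and 79% by the t-test.

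**2. Try the stated δ as a standardised mean difference.** The same formula becomes 2(1.96 + 0.8416)²/δ².

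- δ = 0.5: 62.8, so 63 (t-test 64)
- δ = 0.6: 43.6, so 44 (t-test 45)

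**3. Power by the two-sample t-test, two-sided 5%.**

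| Analysed per arm | δ = 0.5 | δ = 0.6 | 2.0 points, SD 1.9 |
|---|---|---|---|
| 15 | 26% | 35% | 79% |
| 40 | 60% | 75% | over 99% |
| 50 | 70% | 84% | over 99% |

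The row for 40 applies only if all 20 are lost after randomisation and split evenly: (100 − 20)/2 = 40.

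**4. Let controls change.** If the between-arm difference is smaller than the 2.0-point gain, with SD 1.9:

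- 1.5 points (0.79 SD): 55% power at 15 per arm
- 1.0 point (0.53 SD): 29% at 15 per arm and 64% at 40 per arm

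**5. Smallest effect with 80% power (t-test).**

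- 50 per arm: 0.566 SD; × 1.9 = about 1.1 points
- 40 per arm: 0.634 SD; × 1.9 = about 1.2 points

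The conversion to points holds only if 1.9 is the SD of the outcome analysed. If it is the SD of a single score, the SD of the change is 1.9·√(2(1 − ρ)), and ρ is not given.

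**6. Refusals.** The Screening section places consent at first contact, before the baseline assessment, and the Design section fixes 50 + 50 in the arms. People who refuse at consent are not among those 100.

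**The case against.** The best defence is that δ is undefined and might be Cohen's f, which for two equal groups is half the standardised difference. The planning values then give 1.0/1.9 = 0.526, inside the stated range, and 15 per arm is about right. This deserves weight, but the text gives no sign of it: it calls δ a treatment effect. It also rescues the sentence only in part. At f = 0.5 (1.0 SD) the t-test needs 17 per arm, and 15 gives 75% power. The reading does nothing for the within-arm gain used as a between-arm effect.

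A reader might go further and infer that even 50 per arm is underpowered once losses occur. The document does not support that as a flat statement. For its own 2.0 points, 40 per arm has over 99% power. At δ = 0.6, 50 per arm gives 84%. At 40 per arm and δ = 0.6, one-sided 5% gives 85%, and the two-sided test passes 80% with baseline adjustment at a correlation of about 0.3, or with a change score at about 0.55. At δ = 0.5 the correlations needed are about 0.60 and 0.68. A change score with a correlation below 0.5 would do worse than the table. Power over the stated range is therefore uncertain, not shown to fail. Nor can all 20 be taken as losses after randomisation, since the text includes refusals.

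Two other inferences also fail. Limitation 3, that "it is highly probable that the cash incentive value may be insufficient to impact wellbeing", does not contradict limitation 7: power is conditional on an assumed effect, and doubt about reaching that effect is a separate caveat. And nothing says that this calculation will size the main trial. The power calculation for that trial is a separate secondary objective, and the progression criteria use only retention and consent.

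**Conclusion.** The concern holds for the statement about 15 per arm. That number belongs to an effect of 1.05 SD. On the ordinary reading of δ as a standardised mean difference, with two-sided 5%, the true power is 26% to 35% rather than 80%, and 64 to 45 per arm would be needed. The 2.0 points serves as a between-arm effect only if controls do not change, which the document does not say. The allowance of 20 pools people lost before and after randomisation.

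The enrolled size is not shown to be inadequate. At 50 per arm analysed, power is 70% at 0.5 and 84% at 0.6; at 40 per arm it is 60% and 75% without any gain from baseline data. These figures rest on the assumed alpha, the reading of δ and, for 40 per arm, on all 20 losses falling after randomisation. The defect is a wrong power statement and undefined inputs, both cheap to correct.

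**What to change.** - Delete the statement that 15 per arm gives 80% power for δ = 0.5–0.6.
- Define δ as a between-arm difference. State alpha, sidedness, the change assumed in the control arm, and whether 1.9 is the SD of the score or of the change.
- Restate the power, for example: with a two-sided 5% test the pilot has 80% power for a between-arm difference of 0.57 SD with 50 per arm analysed and 0.63 SD with 40 per arm (about 1.1 and 1.2 VAS points if 1.9 is the SD of the analysed outcome).
- Count only losses after randomisation against the 50 + 50, and report refusals separately under the consent rate.
- In limitation 7, name the effect size to which the 80% applies.
- Report the between-arm effect as an estimate with its 95% confidence interval.

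The cost is wording only. The Trial status section says that enrolment and follow-up are complete and analysis is underway, so no participants are affected and the change can still shape the reporting. The stated power becomes less favourable.

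### The sample-size sentence ties 15 per arm and 80% power to δ = 0.5–0.6, but 15 per arm follows from its own means and SD, which give 1.05 SD

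*Protocol article*

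**What the plan says.** The Sample size section defines the outcome: "Our primary outcome is pre-post between difference in caregiver wellbeing scores". It then gives the inputs, "Assuming a mean caregiver wellbeing VAS score of 6.5 in M1 versus 8.5 in M5 (SD1.9) in the intervention arm", and the result, "we would need a minimum sample size of *n* = 15 per arm", which is said to "have 80% power to detect a treatment effect of between δ = 0.6–0.5". From this it concludes that a total of 100 is enough for the primary outcome, allowing for 20 people who refuse or are lost. The Design section splits the 100 as 50 and 50. In the Limitations section, item 7 repeats the claim without an effect size: "although study sample size was sufficient to generate 80% power to detect treatment effects".

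The Sample size section does not give alpha, sidedness, the scale of δ, the expected change in the control arm, or the correlation between baseline and endline scores. The Statistical analysis section compares the score change from M1 to M5 between arms by linear regression, and adds baseline variables as covariates where the arms differ.

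**The concern.** One sentence carries two effect sizes that differ by almost a factor of two. The means and SD imply about 1.05 SD, while the sentence names δ = 0.5–0.6. Required sample size varies with the inverse square of the effect, so a single n cannot serve both.

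The stated power will be used when the results are read. The wellbeing difference is listed first among the primary objectives, and the Trial status section says analysis is under way. If the sentence stands, a null result could be taken as a well-powered negative finding at half a standard deviation. A secondary objective is a power calculation for the large-scale trial. If the pairing of 15 per arm with δ = 0.5–0.6 were carried into it, that trial would be far too small.

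**Working it through.** **Inputs from the Sample size and Design sections.** Means 6.5 and 8.5, SD 1.9, power 80%, 1:1 allocation, N = 100, 20 refusals or losses, δ = 0.5–0.6.

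**Assumptions, because the sections do not say.** Two-sided 5% (one-sided shown as the range); δ standardised; no change in controls; SD 1.9 applies to the change score.

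**1. Reproduce n = 15.** The effect is d = (8.5 − 6.5)/1.9 = 1.053. The normal approximation is n per arm = 2(1.960 + 0.842)²/d² = 15.70/1.108 = 14.2, rounded up to 15. The t-based answer is 15.2, rounded up to 16. So the stated n comes from the means and SD. Its power at 1.05 SD is 82% (normal) or 79% (t).

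**2. The n needed at the stated δ.** The same formula gives 15.70/0.25 = 62.8, so 63, at δ = 0.5, and 15.70/0.36 = 43.6, so 44, at δ = 0.6. The t-based answers are 64 and 45.

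**3. Power at the stated δ (two-sample t, 5%).**

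| Analysed per arm | δ = 0.5, two-sided | δ = 0.6, two-sided | δ = 0.5, one-sided | δ = 0.6, one-sided |
|---|---|---|---|---|
| 15 | 26.2% | 35.5% | 37.9% | 48.3% |
| 40 (100 less 20, equal loss) | 59.8% | 75.5% | 71.6% | 84.5% |
| 50 | 69.7% | 84.4% | 79.9% | 90.9% |

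At 1.05 SD, two-sided power is above 99% with either 40 or 50 per arm.

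**4. Does another reading give 15 at δ = 0.5–0.6?**
- One-sided two-sample test (normal approximation): 50 and 35 per arm.
- Paired or one-sample test: 34 and 24 two-sided; 27 and 19 one-sided.
- δ in raw scale points with SD 1.9: power at 15 per arm falls to 11–14%.
- Use of the baseline score, with δ scaled to the score SD: 15 per arm would need a pre-post correlation r of 0.87 (δ = 0.5) or 0.81 (δ = 0.6) with baseline adjustment, or 0.88 and 0.83 with change scores. No correlation is stated.

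No reading that uses only the stated inputs gives 15.

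**5. What N = 100 can detect.** The smallest difference with 80% power (two-sided 5% t), in SDs of the change score, is 0.63 with 40 per arm and 0.57 with 50. With 15 per arm it is 1.06.

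**6. Conversion to points.** If 1.9 is the SD of a single score, the SD of the change is 1.9 × √(2(1 − r)). That is 2.25, 1.90 and 1.47 for r = 0.3, 0.5 and 0.7. Multiplying by 0.634 gives about 1.4, 1.2 and 0.9 points with 40 per arm.

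**7. Effect of r on power.** If δ is scaled to the score SD and change scores are analysed, 40 per arm has 46–61% power at r = 0.3 and 81–93% at r = 0.7. With baseline adjustment instead (normal approximation), 40 per arm reaches about 80% at δ = 0.6 from r = 0.3, and at δ = 0.5 from r = 0.6.

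**The case against.** The best defence is that only the label δ = 0.5–0.6 is wrong. The n does reproduce from the explicit means and SD, δ is never defined, and the sources cited beside it are not at hand. On the 1.05 SD reading, N = 100 is ample, and Limitation 7, which names no effect, is true. This stands to the extent that the document does not show which of the two effects was the intended target. It does not rescue the sentence, which still attaches 80% power at 15 per arm to an effect for which that n has 26–35%.

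A reader might go further and infer that the trial falls short of 80% power at its own δ. The document does not support that as a flat statement. With 50 per arm, power at δ = 0.6 is 84%. With 40 per arm and a one-sided test it is about 85%. With a high pre-post correlation, 40 per arm can exceed 80% across the range; with a low one it falls well below 60–75%. Nor is 40 per arm certain. The allowance of 20 mixes refusals, who may never be randomised, with losses, and multiple imputation is planned if loss is significant.

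A reader might also set the calculation against Limitation 3, which says "it is highly probable that the cash incentive value may be insufficient to impact wellbeing". That is a caveat about the intervention and not a design assumption. What 15 per arm could detect is not what the planned 50 per arm could detect, so there is no contradiction.

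Finally, this is a pilot. Its overall aim is the feasibility of a later trial, and the progression criteria are retention and enrolment only. That lowers the weight of the error. It does not excuse it, because the protocol chose to claim 80% power and repeats the claim.

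**Conclusion.** The sentence is wrong as written. Fifteen per arm belongs to 1.05 SD, given no change in controls and an SD of 1.9 for the change score (r = 0.5 if 1.9 is the SD of a single score). It does not belong to δ = 0.5–0.6, which needs three to four times as many participants. This part is firm under one-sided, paired and raw-scale readings.

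The power of N = 100 at δ = 0.5–0.6 is less certain: 60–75% with 40 per arm and 70–84% with 50 (one-sided 72–85% and 80–91%), all conditional on the assumed test and before the unstated correlation is taken into account. The supported conclusion is that adequacy at δ = 0.5–0.6 is not shown, rather than that the trial is underpowered. The point should be fixed, but it is not critical, since no progression rule uses this power.

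**What to change.** In the Sample size section:
- Delete the pairing of 15 per arm with δ = 0.5–0.6.
- State what N = 100 delivers, with its assumptions: 80% power (two-sided 5%, two-sample t) for a between-arm difference in change scores of 0.63 SD of the change with 40 per arm analysed, or 0.57 with 50.
- If power at δ = 0.5–0.6 is also reported, give it for both 40 and 50 per arm.
- Give a conversion to points only with the correlation assumed: with 40 per arm, about 1.4, 1.2 and 0.9 points for r = 0.3, 0.5 and 0.7.

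In Limitation 7, name the effect size to which 80% power applies.

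The cost is wording only. Enrolment and follow-up are complete and do not change. The power claim becomes narrower, and the secondary-objective power calculation for the large-scale trial starts from a consistent statement.
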